### **Specific Aims**

1. To describe the sociodemographic and clinical features of both family members and ICU patients.
2. To determine the level of anxiety symptoms, depressive symptoms, PTSD symptoms, cognitive impairment, fatigue, perceived social support, resilience, family satisfaction, and caregiver burden among family members of ICU survivors of a public hospital in Chile.
3. To explore the association between contextual factors, primary stressors, secondary stressors, psychosocial resources, and PICS-F impairments among family members of ICU survivors of a public hospital in Chile.
4. To evaluate the extent to which secondary stressors (family satisfaction or caregiver burden) significantly contribute to PICS-F impairments among family members of ICU survivors of a public hospital in Santiago, Chile.

**Hypotheses:** The proposed hypotheses for the study are:

1. Family members of ICU survivors will experience at least one PICS-F impairment at three and/or six months after hospital discharge.
2. Primary stressors (anxiety, depressive, PTSD symptoms, fatigue, or cognitive impairment) and/or psychosocial resources (social support or resilience) will be associated with at least one PICS - F impairment at three and/or six months after hospital discharge.
3. After controlling for contextual factors, primary stressors, and psychosocial resources, at least one secondary stressor (family satisfaction or caregiver burden) will significantly contribute to the development of at least one PICS - F impairment at three and/or six months after hospital discharge.

### **SCIENTIFIC NOVELTY**

Reduction in mortality rates in the last decades has shifted the attention to PICS, with researchers identifying several challenges related to survivorship. Nonetheless, long-term issues faced by ICU family members remain poorly understood. ICU clinicians and researchers have started to understand that critical illness is not limited to the ICU or hospital setting but is part of the trajectory of a disease that has not been fully explored yet. This study will be one of the first to comprehensively explore all PICS-F impairments simultaneously utilizing the Caregiver Stress Model (CSM). Although Cameron et al. employed the CSM, their study did not include family satisfaction as a secondary stressor, resilience as a psychological resource, and they did not measure PICS-F cognitive impairment. Despite PICS-F awareness, physical and cognitive impairments have been disproportionately less studied. This study will advance knowledge regarding the incidence and factors related to PICS-F physical impairment and will provide initial data on the cognitive impairment that family members of ICU survivors may experience.

Besides, this study will be one of the first to explore how each of the PICS-F impairments is affected by variables and constructs measured during the ICU stay and nearly after ICU discharge. As stated by

Johnson et al. "... an unknown premorbid functioning could create the inability to distinguish between incident and preexisting symptoms" observed in PICS-F impairments. The scientific novelty of this study is also grounded in the inclusion of caregiver burden as a secondary stressor that may impact PICS-F impairments. Although evidence on caregiver burden in family members of ICU survivors is emerging, the development of PICS-F impairments may not be solely explained by the residual effect of a traumatic event such as an ICU admission but also, by the burden of providing care to an ICU survivor. Although common issues and mechanisms may be found between caregivers of ICU survivors and caregivers of patients with different diseases (e.g., Alzheimer's disease, dementia), the acute onset of critical illness and the experience of an ICU stay may significantly impair caregiver's psychological, physical, and mental future resources required to assume the caregiver role after hospital discharge. In other words, the chronic nature and slower progression of patient's impairments in other caregiver populations may have less impact on caregiver burden by allowing a progressive adaptation of the caregiver to new tasks and strains.

ICU survivorship has imposed a significant burden on the healthcare system, society, and particularly caregivers of those who endure a critical illness. In Chile, around 66% of hospital beds attend poor and middle-class citizens. Therefore, findings from this study conducted in a public hospital will generate data for local healthcare providers such as similar ICUs, hospitals, and the primary care network providing care to family members of ICU survivors. Results from a study also will inform tailored interventions that account for the particular features of the caregiving process of an ICU survivor, particularly the influence of the stage (e.g., ICU hospitalization) that precedes the caregiving role. Finally, this study will provide valuable data on incidence and related factors of PICS-F that are currently unknown, particularly, among Chilean family members of ICU survivors, and will provide data and research experience to conduct larger multicentric studies to validate the findings of this study.

## METHODS

**Design:** This is a quantitative, analytical, and prospective cohort study that considers four times of measurement:

- T1 → Between the 3rd – 7th day of ICU admission (enrollment)
- T2 → Nearly after ICU discharge
- T3 → 3 months after hospital discharge
- T4 → 6 months after hospital discharge

**Setting:** The study will be conducted in an adult ICU of a high complexity hospital (> 400 beds) belonging to the Southeast Metropolitan Health Service of Santiago, Chile. This hospital provides care, along with other centers, to a population of around 1.700.000 subjects. This hospital ICU comprises 24 beds with an average of 550 patients admitted during 2019-2020. Visiting policy includes usually 2 hours from Monday to Thursday with flexibility in special cases such as dying patients, collaboration in recovery, or with added caregiving requirements during ICU stay.

## Subjects

**Inclusion criteria:** All adult family members (≥ 18 years old) identified as the patient's representative, Spanish speakers, and likely to become responsible for providing or coordinating care after hospital discharge will be eligible. Besides, the family member's ICU patient must have at least 48 hours in the ICU, be > 18 years old, and receive respiratory support (noninvasive ventilation, high-flow nasal cannula, or invasive mechanical ventilation).

**Exclusion criteria:** Family members of ICU patients with a high impending death risk or likely to be discharged from the ICU in the following 24 hours after screening will be excluded. Family members will be withdrawn at any point of the study if the patient dies.

**Variables:** To explore PICS-F impairments incidence and the potential associations with other variables, the following independent variables measured through questionnaires will be used:

- **Anxiety and Depressive Symptoms:** The Patient Health Questionnaire for Depression and Anxiety (PHQ-4) is an ultra-brief screening tool utilized to explore the occurrence of anxiety and depressive symptoms according to the DSM – IV criteria. PHQ-4 comprises 4 items for cardinal symptoms of both anxiety (2 items) and depressive (2 items) disorders. Answers are scored utilizing a Likert scale ranging from 0 ("Not at all") to 3 ("Nearly every day"). A cut-off value of 6 points for the sum of all items (PHQ-4 ≥ 6) has been utilized to identify subjects with a potential anxiety/depressive disorder. The Chilean-Spanish

version of the PHQ-4 has shown an adequate internal consistency. PHQ-4 will be used in all 4 time points of the study.

- **Posttraumatic stress disorder symptoms:** The Impact of Event Scale-Revised (IES-R) is a 22-item questionnaire aimed to measure the degree of suffering associated with a traumatic event in the form of subjective stress. IES-R items are presented in a Likert scale ranging from 0 ("Not at all") to 4 ("Extremely") and an overall score is calculated by averaging all items. Higher scores reflect a higher presence of PTSD symptoms. The Chilean-Spanish version of the IES-R has shown good reliability. For this study, the 6-item version (IES-6) of the IES-R will be utilized, which comprises items 3, 6, 11, 12, 18, and 21 of the original scale. A cut-off average score of 1.75 ( $IES-6 \geq 1.75$ ) has been used to identify family members likely to have a PTSD diagnosis. Since PTSD symptoms are usually measured after the traumatic experience (ICU admission/stay), IES-6 will be applied at T2, T3, and T4.
- **Perceived Social Support:** The Medical Outcomes Study Social Support Survey (MOS-SSS) was developed to measure the perception of availability of emotional, instrumental, and informational resources by the individual's social network and includes 18 items with a five-point Likert-type response from 1 ("none of the time") to 5 ("all of the time"). MOS-SSS has shown an adequate internal consistency for its Chilean-Spanish version. For this study, the modified 8-item version (mMOS-SSS) of the MOS-SSS will be utilized, which comprises items 2, 5, 7, 12, 15, 17, 19, and 20 of the original scale. An overall score for the mMOS-SSS is calculated by converting Likert-type responses to a zero to 100 scale and then averaging them. mMOS-SSS will be utilized in all 4 time points of the study.

- **Patient's Dependency:** The Barthel Index (BI) is an extensively utilized ordinal scale that aims to evaluate a subject's functional independence regarding activities of daily living such as dressing, transfer, bathing, feeding, toilet use, and use of stairs. BI includes 10 items, each with 2 to 4 alternatives depending on the case which are scored on a 5 points intervals scale (e.g., 0, 5; 0, 5, 10; 0, 5, 10, 15). An overall score can be obtained by summing all items, with higher scores reflecting higher functional independence. The BI has reported an adequate internal consistency. BI will be completed by the patient's responsible family member at T1 regarding the patient's functional independence status before ICU admission. Then, BI will be applied at T2, T3, and T4.
- **Family Satisfaction:** The Family Satisfaction with Care in the Intensive Care Unit – 24 (FS ICU-24) questionnaire is a widely used tool to explore the family member's evaluation of their ICU experience in terms of communication with ICU health care providers, emotional support, closeness to the patient, ICU environment, decision-making involvement, and quality of nursing care of the patient. FS ICU-24 has

24 items with a Likert-type response scale from 1 ("Excellent") to 5 ("Poor"). In this study, the three open-ended questions of FS ICU-24 will not be applied to decrease participant burden. To obtain scores for overall satisfaction, Likert-type responses are transformed to a numeric scale (range: 0–100) and then averaged, with higher scores indicative of higher levels of satisfaction. The Chilean-Spanish version of the FS ICU-24 has shown a high internal consistency. FS ICU-24 will be only applied at T1 and T2.

- **Caregiver Burden:** The Zarit Burden Interview (ZBI) was developed to subjectively measure the burden of caring for an adult with a disabling condition. ZBI is composed of 22-items with a Likert scale extending from 1 ("never") to 5 ("nearly always") with higher scores reflecting a higher level of burden. The Chilean Spanish version of the ZBI has reported an adequate internal consistency. In this study, the 7-item version of the ZBI will be employed which includes items 2, 3, 6, 9, 10, 17, and 22 of the original questionnaire. A cut-off value of  $\geq 17$  points for the sum of all 7 items has been established to classify subjects with intense caregiver burden. Caregiver burden will be measured only in T3 and T4.

All questionnaires in this study are self-reported and the average time for completing them, including the MEFO test, is estimated in 50-55 minutes. Besides, relevant family members' sociodemographic variables plus demographic and clinical data from the patient will be collected at each time point. Detailed information on these variables is presented in the statistical analyses section (Table 1).

**Outcome:** To determine the presence of each PICS-F impairment, four dichotomous dependent variables will be defined: psychological (PHQ-4  $\geq 6$  or IES-6  $\geq 1.75$ ), physical (SF-36 VT  $< 45$ ), and cognitive (MEFO  $< 9$ ) impairments at T3 and T4. Subjects scoring above or below the respective cut-off value will be categorized as having PICS-F in the respective impairment at T3 and/or T4.

**Statistical analyses:** To explore and characterize data, descriptive statistics will include the analysis of summary statistics and plots (e.g., histograms, q-q plots, and boxplots). Continuous normally distributed variables will be reported using means and standard deviations (SD) and non-normally distributed variables with medians and interquartile range (IQR). Categorical variables will be reported using frequency and percentages. For each questionnaire, internal consistency will be explored calculating Cronbach's alpha.

The incidence of each PICS-F impairments (psychological, physical, and cognitive) at T3 and T4, will be determined by classifying subjects according to the proposed cut-off scores. The number of subjects showing a given PICS-F impairment will be divided by the total number of subjects at the specific point of the study. Then, to analyze factors associated with PICS-F impairments, bivariate and multivariate analyses will be conducted. Cross-sectionally, Chi-square or Fisher's exact test will be applied in case of analyzing two or more categorical variables. In the case of two continuous numerical variables, Pearson or Spearman correlation test will be used. If one dependent variable is continuous normally distributed and the independent variable is categorical, then a t-test (two groups) or ANOVA test (three or more groups) will be applied; if the dependent variable is non-normally distributed, Mann-Whitney U test (two groups) or Kruskal-Wallis test (three or more groups) will be applied. Bivariate analyses, along with factors identified in the literature, will help to identify potential independent variables for multivariate models.

Given that this study considers more than one measurement (repeated measures) over time, this information should be considered as correlated within-subjects. Therefore, to analyze variables associated with the PICS-F impairments over time, panel or longitudinal analysis will be used. First, graphical methods, such as panel line plots, will be used to visualize the trend and variation between and within-subjects over time. This analysis will be useful for determining some important covariates and the regression models to be included and applied afterward. Second, the strength of outcome correlation should be defined to decide the regression methods. In this scenario, and considering the nature of the outcome, generalized linear mixed models (GLMM) will be used. Contextual factors (family member and patient features) of each subject will be considered fixed effects, but random effects will be included because it is expected that the outcome in each time and for each subject will vary. Given that the outcome is measured as a dichotomous variable, the family will be binomial, and the link function is expected to be logit. Then, the model will be built starting with a large model and trimming it down according to statistical significance but also based on the proposed theoretical model (CSM). The initial models proposed for this study are presented in Table 1.

If family satisfaction (FS) or caregiver burden (CB) is associated with any of PICS-F impairments at T3 and/or T4, GLMM with and without the selected secondary stressor will be fitted to analyze the extent of this association. First, FS measured at T1 will be added to models 1-4 while the FS measure at T2 will be included in models 5-8. Similarly, CB measured at T3 will be included in models 9-20 while the T4 measure of CB will be added to models 17-20. The original model without a secondary stressor will be contrasted

with the same model plus the secondary stressor (either FS or CB). Scores such as Akaike Criterion and likelihood ratio tests will be performed and residual plots will be obtained. Also, 95% confidence intervals will be reported and a  $p$ -value  $< .05$  will be considered statistically significant. All statistical analyses will be conducted in R, using the applicable packages.

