| 7                     |                                                                                             | experience, income,                                                                                        | X     | X     | X        | X    | X        | X    |                                              |                | X        |      |
| 8                     |                                                                                             | employment status                                                                                          | X     | X     | X        | X    | X        | X    |                                              |                |          | X    |
|                       | T 3 - 3 months after hospital discharge                                          |                                                                                                            |       |       |          |      |          |      | T 3                               |                |          |      |
|                       | Patient                                                                                     | Family member                                                                                              | PHQ-4 | IES-6 | mMOS-SSS | BRCS | SF-36 VT | MEFO | PHQ-4                                        | IES-6          | SF-36 VT | MEFO |
| 9                     | Age, COVID-19 diagnosis, ICU and hospital LOS, hospital readmission, discharge location, BI | Age, gender, education, kinship, MHA, previous ICU experience, income, employment status, caregiving hours |       | X     | X        | X    | X        | X    | X                                            |                |          |      |
| 10                    |                                                                                             |                                                                                                            | X     |       | X        | X    | X        | X    |                                              |                | X        |      |

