|                       |                                                                                             | T 4 - 6 months after hospital discharge                                                         |       |       |          |      |          |      |                                              | T 4 |          |      |
|                       | Patient                                                                                     | Family member                                                                                              | PHQ-4 | IES-6 | mMOS-SSS | BRCS | SF-36 VT | MEFO | PHQ-4                                        | IES-6          | SF-36 VT | MEFO |
| 17                    | Age, COVID-19 diagnosis, ICU and hospital LOS, hospital readmission, BI, discharge location | Age, gender, education,                                                                                    |       | X     | X        | X    | X        | X    | X                                            |                |          |      |
| 18                    |                                                                                             | kinship, MHA, previous ICU                                                                                 | X     |       | X        | X    | X        | X    |                                              | X              |          |      |
| 19                    |                                                                                             | experience, income,                                                                                        | X     | X     | X        | X    |          | X    |                                              |                | X        |      |
| 20                    |                                                                                             | employment status, caregiving hours                                                                        | X     | X     | X        | X    | X        |      |                                              |                |          | X    |

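### No listed item records whether the relative already cared for the patient before admission, so part of any burden-impairment association may reflect long-standing caregiving rather than care that began after the ICU stay

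*Protocol*

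**What the plan says.** - **Burden.** The Variables section uses the 7-item Zarit interview and says "Caregiver burden will be measured only in" T3 and T4.
- **Caregiving hours.** For the relative's variables the protocol refers the reader to Table 1: "Detailed information on these variables is presented in the statistical analyses section (Table 1"). The T3 block (models 9-16) ends its list with "previous ICU experience, income, employment status, caregiving hours", and the T4 block (models 17-20) also ends with "employment status, caregiving hours". The T1 and T2 blocks list age, gender, education, kinship, mental health antecedents, previous ICU experience, income and employment status. They contain nothing on caregiving.
- **Eligibility.** The relative must be "likely to become responsible for providing or coordinating care after hospital discharge". Existing caregivers are neither excluded nor flagged.
- **Pre-ICU information.** At T1 the relative reports the patient's Barthel Index as it was before admission. Table 1 lists a Barthel Index in the T1 block (models 1-4). The T3 and T4 blocks list one under their own time headings.
- **Use of burden.** The Statistical analyses section adds T3 burden to models 9-20 and T4 burden to models 17-20. Each model is compared with and without burden by Akaike criterion and likelihood ratio test, at p < .05.
- **Interpretation.** The Theoretical Framework places burden after hospital discharge. Hypothesis 3 concerns its contribution to the development of impairment. Scientific Novelty argues that impairment may be explained in part "by the burden of providing care to an ICU survivor", and contrasts this with other conditions, whose slower course limits burden "by allowing a progressive adaptation of the caregiver to new tasks and strains".

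**The concern.** The reason given for including burden is that caregiving after critical illness starts abruptly. The cohort can nevertheless contain relatives who had cared for the same patient for years. Such a relative may report high burden at T3 and also have poor psychological or physical health, whatever the ICU stay added. Prior caregiving would then be a common cause of exposure and outcome in the models that test Hypothesis 3, and the burden odds ratio would tend to be too large.

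Scientific Novelty already cites the warning that unknown premorbid functioning blurs incident and pre-existing symptoms, but the plan does not apply this reasoning to burden. An analysis plan cannot repair the gap later. If the item is not asked at T1, the only substitute is recall months afterwards, when the caregiving role has changed.

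**Working it through.** **1. What is recorded, and when**

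| Item | T1 | T2 | T3 | T4 |
|---|---|---|---|---|
| Burden (7-item Zarit) | no | no | yes | yes |
| Caregiving hours (Table 1) | no | no | yes | yes |
| Patient's Barthel | pre-ICU status | current | current | current |
| Relative's care before admission | no | no | no | no |

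The Data collection section uses the relative's participation in care at T3 and T4 to decide whether caregiving measures are taken. It does not ask about care before admission.

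**2. Sample size used for illustration**

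The protocol's own chain is:
- 1.96² × 0.20 × 0.80 / 0.05² = 245.9, so 246 (stated 247).
- 600 × 247 / (600 + 247) = 174.97, so 175.
- 175 / (1 − 0.40) = 291.7, so 292.

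It reproduces within rounding. The illustrations use n = 175. The point does not depend on these figures.

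**3. Simple illustration (all effect inputs assumed)**

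Let C = 1 for a prior caregiver.
- Burden = 1.0 × C + N(0,1)
- Pre-ICU Barthel = −1.0 × C + N(0,1)
- logit P(impairment) = −1.6 + 1.1 × C

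The odds ratio for C is e^1.1 = 3.0, and burden has no effect of its own. There were 600 replicates per row, with a 5% likelihood ratio test for burden. Cells show rejection rate and odds ratio per SD.

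| Share of prior caregivers | Burden alone | + pre-ICU Barthel | + prior-caregiver flag |
|---|---|---|---|
| 10% | 11.8%, 1.12 | 10.5%, 1.10 | 6.7%, 0.99 |
| 20% | 21.3%, 1.21 | 18.3%, 1.18 | 4.8%, 1.01 |
| 30% | 24.7%, 1.23 | 18.8%, 1.20 | 5.0%, 1.01 |
| 40% | 29.5%, 1.25 | 21.8%, 1.21 | 4.8%, 1.00 |

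The Monte Carlo standard error at 5% is √(0.05 × 0.95 / 600) = 0.9 percentage points, so the last column is compatible with the nominal level. The table shows the mechanism and how little the Barthel proxy removes. It overstates the size for this protocol, because models 9-20 carry further covariates.

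**4. Illustrations closer to models 9-20**

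Assumed: n = 175, 30% prior caregivers, burden 0.5-1 SD higher and impairment odds 2-3 times higher in prior caregivers, no true burden effect. The ranges run over these settings.
- *Adjusting for caregiving hours, Barthel and two concurrent symptom scores, all related to prior caregiving:* odds ratio 1.05-1.22, false positives 7-18%. Adding prior-caregiving status gives 0.99-1.00 and 6-7%.
- *Adjusting for caregiving hours (1-1.5 SD higher in prior caregivers) and three concurrent symptom scores (0.5 SD higher), without Barthel, 1500 replicates:* odds ratio 1.04-1.18, false positives 6-12%, against 1.08-1.26 and 7-23% unadjusted. The mildest setting gives 1.04-1.06 and about 6%.

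Taken together, the residual odds ratio is about 1.04-1.22 and the false-positive rate about 6-18%.

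**The case against.** **Existing covariates absorb much of this.** Models 9-20 already list caregiving hours, concurrent Barthel, readmission, discharge location, kinship, mental health antecedents, employment, social support, resilience and most concurrent symptom scores. This stands in part: the fuller illustrations show a smaller bias, close to none in the mildest setting, but not its removal across the range.

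**The pre-ICU Barthel identifies many new caregivers.** This also stands in part. A patient who was fully independent probably had no caregiver, so a reader who infers that prior and new caregivers cannot be told apart at all goes too far. But the index describes the patient's function, not whether this relative gave the care. Table 1 does not list the pre-ICU value where burden is tested, although the data will exist and could be added.

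**Baseline health is measured.** PHQ-4, vitality, social support and resilience are recorded at T1 and could be carried forward. They would help, but they are measured during the ICU crisis and do not show caregiving status.

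**The study is exploratory and does not promise a new-caregiver effect.** This is fair. The burden of caring for an ICU survivor includes continuing caregivers, the contrast in Scientific Novelty is with caregivers in other diseases, and models 9-16 are cross-sectional in any case. The objection limits the point to interpretation. It does not remove it, because Hypothesis 3 speaks of development of impairment and burden is tested at p < .05.

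**All effect inputs are assumed.** This stands in full.

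**Conclusion.** The point holds as a gap in data collection that limits how the burden result can be read. The documents settle the facts: burden and caregiving hours are recorded only at T3 and T4, existing caregivers may enrol, and no listed item records care given before admission.

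The size is not settled. It depends on the share of prior caregivers and on how strongly prior caregiving relates to burden and impairment, and the protocol gives none of these. The residual odds ratio of about 1.04-1.22 with false-positive rates of about 6-18% is conditional on the assumed inputs, and its lower end is negligible.

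A reader might infer that any burden finding will be spurious, or that long-standing burden will simply be credited to post-ICU care. The documents do not support that: the planned covariates and the pre-ICU Barthel take up part of the confounding, and a true burden effect may exist. The incidence estimates and the sample size are unaffected. The change is worth making because it is cheap and the information is hard to recover later.

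**What to change.** 1. At T1, add one item on care given to this patient before admission: yes or no and, if yes, hours per week, phrased like the caregiving-hours item used at T3 and T4.
2. Enter that item, together with the pre-ICU Barthel Index already collected at T1, as covariates in models 9-20 wherever burden is tested, in both the model with burden and the model without it.
3. Describe burden and each impairment separately for new and continuing caregivers.
4. Limit any statement about burden arising from post-ICU caregiving to the adjusted estimate.

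Cost: one more question at T1 in a battery of 50-55 minutes, and one or two more parameters in models that are already large. No extra visit, staff or instrument is needed, and the sample size calculation does not change.
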